**Time-to-Event outcomes**

Cumulative Live Birth Rate (CLBR) and Cumulative Pregnancy Rate (CPR) will be analyzed as time-to-event outcomes, defined as the proportion of participants achieving a live birth or pregnancy within three years following initiation of treatment. Kaplan–Meier curves will be used to display cumulative incidence, and groups will be compared with stratified log-rank tests. Treatment effects will be estimated using Cox proportional hazards models, stratified by center and adjusted for prespecified covariates. Hazard ratios with 95% confidence intervals will be reported.

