# WHY THIS TRIAL IS NEEDED

BACKGROUND

Endometriosis

Endometriosis is a prevalent condition affecting 10% of female population of reproductive age, leading to pain and subfertility (1). An earlier systematic literature review and meta-analysis suggests that women with advanced endometriosis (revised American Society for Reproductive Medicine classification of endometriosis (rASRM) stage III-IV) have a lower likelihood of achieving clinical pregnancy/live birth compared to women without endometriosis, while this difference has not been observed for mild disease (stage I-II) (2).

Gynecological Ultrasound and staging

The prevalence of endometrioma and deep endometriosis found through systematic transvaginal ultrasound on women referred for ART treatment in Sweden has been estimated at 21.8% (3). Additionally, 75.8% of those with endometriosis were unaware of their condition prior to diagnosis (3). In recent years, two staging systems, namely the American Association of Gynecologic Laparoscopists (AAGL) Endometriosis classification (4, 5) and #ENZIAN (6) have gained prominence owing to their accuracy when juxtaposed with surgical findings.

Surgical Treatment

Women with endometriosis seem to experience pain relief after bowel surgery due to endometriosis (7, 8). Consensus from the European Society of Human Reproduction and Embryology (ESHRE) indicates that surgery can be performed prior to treatment with assisted reproductive technologies (ART) (7). Additionally, the number of spontaneous pregnancies is high after surgery on patients with deep endometriosis (10). Furthermore, in patients with endometriosis stage I-II or in infertile patients with endometriomas, surgery can in some cases be considered to improve fertility (7-9). However, the risk of severe complications in patients undergoing rectal surgery is up to 10% including anastomosis leakage and fistulas (10, 11).

Fertility treatment

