# STUDY OBJECTIVES

HYPOTHESIS

First line surgery (prior to ART treatment) in women with endometriosis AAGL stage III-IV will result in improved cumulative live birth rate (CLBR) as compared to first line ART.

PRIMARY OBJECTIVE

To assess whether surgery conducted prior to ART in women with endometriosis AAGL stage III-IV increases chances of CLBR as compared to first line ART.

.

SECONDARY OBJECTIVES

To evaluate whether surgery prior to ART treatments in women with endometriosis AAGL stage III-IV will result in improved cumulative pregnancy rate (CPR) and lower miscarriage rate as compared to first line ART.

To compare whether surgery prior to ART treatments in women with endometriosis AAGL stage III-IV will result in shorter time to live birth or pregnancy as compared to first line ART.

To investigate if surgery prior to ART treatments in women with endometriosis AAGL stage III-IV will result in better reproductive outcomes per IVF cycle and a lower rate of recurrent implantation failure (RIF).

To assess if surgery prior to ART treatments in women with endometriosis AAGL stage III-IV will result in lower rate of infections after oocyte pick-up requiring treatment with antibiotics as compared to first line ART?

To evaluate if surgery prior to ART treatments in women with endometriosis AAGL stage III-IV result in higher Quality of life and less pain measured with Endometriosis Health Profile (EHP-30) and Numeric Rating Scale (NRS) before ART, i) at the time of oocyte retrieval, ii) two months after ART and iii) at the three-year follow-up visit as compared to first line ART.

To explore whether surgery prior to ART treatments in women with endometriosis AAGL stage III-IV will be cost effective compared with first line ART?

To examine if surgery prior to ART treatments in women with endometriosis AAGL stage III-IV will result in reduced pregnancy and delivery complications, as well as fewer complications within 8 weeks postpartum, compared to first line ART.

To investigate whether serum progesterone level on the day of frozen embryotransfer in hormone replacement cycles in patients with severe endometriosis is associated with reproductive outcomes (LBR, pregnancy rate, miscarriage rate) and to determine if there is any difference in p-progesterone level between the two different study groups first line ART vs first line surgery in women with endometriosis AAGL stage III-IV?

PRIMARY OUTCOME MEASURE

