Cumulative live-birth rate within three years from first treatment (surgery or ART treatment).

Definition of primary outcome measure

CLBR is defined as any live births from first treatment until end of follow up (three years from first ART treatment or surgery or drop out from the study, whichever comes first).

Primary outcome will be calculated considering also the following pre-specified subgroups: study center,  type of ART-treatment (IVF or ICSI), age (< and > 35 years), ovarian reserve ( anti-mullerian hormone (AMH) <0.5ng/L, 0.5-3.5 ng/L and AMH >3.5ng/L ) (35) adnexal surgery (yes/no), surgery on deep endometriosis anterior compartment (yes/no) or deep endometriosis posterior compartment (yes/no) (defined by Classification of surgery, “Klassifikation av vårdåtgärder” (KVÅ codes), see appendix).

SECONDARY OUTCOME MEASURE

- Cumulative Pregnancy Rate (CPR)
- Time to pregnancy and live birth
- Spontaneous Pregnancy Rate
- Miscarriage rate and/or extrauterine pregnancies
- Reproductive outcomes per IVF cycle
- Rate of recurrent implantation failure (RIF), (20) evaluated at the end of the study period
- Infections after oocyte pick-up
- Quality of life and pain
- Peri- and two months postoperative complications classified by Clavien-Dindo and Classic systems
- Health care costs
- Obstetrical outcomes and complications
- P-progesterone levels on day of embryo transfer at first HRT frozen-thawed artificial embryo transfer cycle

Definition of secondary outcome measures

Cumulative Pregnancy Rate (CPR) is defined as all pregnancies confirmed with ultrasound, from first treatment (surgery or ART) until three years of follow up.

Time to pregnancy is defined as time from first treatment (surgery or ART) to first pregnancy confirmed with ultrasound. Time to live birth defined as time from first treatment (surgery or ART) to first livebirth.

Spontaneous pregnancy rate is defined as any spontaneous pregnancy occurring between first treatment and end of follow-up.

Miscarriage rate defined as frequency and proportion of spontaneous loss of any clinical and biochemical pregnancy before week 22 and/or extrauterine pregnancy defined as a pregnancy not located in the uterine cavity, occurring between first treatment and end of follow-up.

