In Sweden in 2023, 9.9% of patients undergoing surgery for endometriosis within the framework of national highly specialized care experienced mild complications Clavien Dindo 1-2 (e.g. infection and hematoma at the surgical site), and 3.3% experienced serious complications Clavien Dindo 3 (e.g. bowel leakage, unexpected bladder injury, ureteral injury, or intra-abdominal bleeding requiring reoperation) (38). Serious complications may, in rare cases, necessitate further surgical interventions. The risk of complications varies slightly depending on the location of the endometriosis (38).

Patients undergoing surgery will need to delay ART treatment by two to three months in order to fully recover.

FERTILITY TREATMENT WITH ART

ART treatments will be carried out at Swedish reproductive units authorized to provide publicly funded fertility care. The majority of treatments are expected to take place at the university-affiliated reproductive clinics in Stockholm, Gothenburg, Skåne, and Uppsala. However, for participants residing in other regions of Sweden, undergoing treatment locally offers a significant advantage by reducing the logistical and emotional burden of long-distance travel to these central clinics. To ensure equitable access and minimize patient stress, regional ART centers will be considered when appropriate.

One IVF/ICSI-cycle is defined as the transfer of all the embryos created via that particular oocyte pick-up until pregnancy confirmation or until the failure of the last embryo transfer. In case of a cancelled cycle prior to oocyte pick-up it will not be counted. The duration of one IVF-cycle depends on the number of embryo transfers and typically ranges between two and nine months.

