**Additional analysis**

– Exploratory subgroup analyses will not be adjusted for multiplicity.

– Safety outcomes will be summarized descriptively by treatment group (frequency, severity, relation to treatment).
– All available data will be used, including outliers.
– Missing outcome data will be handled under the missing-at-random assumption via maximum likelihood in mixed models; for regression models requiring complete covariates, complete-case analysis will be applied.

Covariates

Primary and secondary outcomes will be adjusted for prespecified covariates (age, BMI, AMH, ART type, center), chosen based on clinical relevance and prior evidence.

POWER CALCULATION AND SAMPLE SIZE

The sample size calculation was based on a two-sample comparison of proportions with a two-sided α=0.05 and 80% power. Based on observational data (18, 19), the cumulative live birth rate (CLBR) after three IVF cycles was assumed to be 55% in the ART-only group and 71% in the surgery+ART group (relative risk ≈1.29). This yields a required sample size of 142 participants per arm (284 total). Allowing for 20% attrition, the planned total sample size is 350 participants.

The necessary sample size for this study is estimated to 323 patients to accommodate a statistical analysis method. This estimation uses the 'pwr' package in R, specifically employing the power.prop.test method, which is designed to compare two proportions. This method is more aligned with contemporary statistical practices and provides a clear, transparent methodology for determining the required sample size based on expected success rates.

This means inclusion of 29 patients from/each center/year and 15 surgeries/year. In a Swedish study published in 2022 the prevalence of endometriosis in patients referred for ART-treatment was 21.8% and 17.2% of women had DE (14). In 2021 almost 10 500 IVF cycles were performed in Sweden, while more than 5 500 of those were first-time IVF/ICSI with autologous gametes ((46) Figure 22).

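### Cumulative pregnancy rate is defined as a three-year proportion but compared only by log-rank and Cox, which cannot separate fewer women pregnant from women pregnant later

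*Protocol*

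**What the plan says.** In the protocol's STATISTICAL CONSIDERATIONS, under Time-to-Event outcomes, CLBR and CPR are both "defined as the proportion of participants achieving a live birth or pregnancy within three years following initiation of treatment". The same paragraph gives Kaplan-Meier curves for display, and for comparison says that "groups will be compared with stratified log-rank tests. Treatment effects will be estimated using Cox proportional hazards models". No other section gives a test for CPR. Primary analysis covers the three-year live-birth proportion only, and Cycle-Specific Outcomes covers rates per IVF/ICSI cycle.

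STUDY OBJECTIVES keeps rate and timing apart. One secondary objective asks whether surgery "will result in improved cumulative pregnancy rate (CPR) and lower miscarriage rate as compared to first line ART"; the next asks about a shorter time to pregnancy or live birth. The definitions are separate too: "Cumulative Pregnancy Rate (CPR) is defined as all pregnancies confirmed with ultrasound, from first treatment (surgery or ART) until three years of follow up", and "Time to pregnancy is defined as time from first treatment (surgery or ART) to first pregnancy confirmed with ultrasound".

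On timing, DEFINITION START OF TRIAL sets time zero at surgery or at the start of FSH injections, and STUDY TREATMENT states: "Patients undergoing surgery will need to delay ART treatment by two to three months in order to fully recover".

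**The concern.** The CPR question is how many women are pregnant by three years. The log-rank null is that the two curves coincide throughout, and a Cox hazard ratio summarises the effect on the assumption that the hazards stay proportional. In this trial the surgery arm has a known period after time zero in which ART pregnancies cannot occur. If surgery changed nobody's final result, its curve would still start lower and catch up.

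Two misreadings follow. An unchanged three-year rate could be reported as a worse CPR after surgery. A true gain could appear as a non-significant hazard ratio pulled towards 1. CPR is the first-listed secondary outcome, and the protocol intends the results to inform national guidelines, where fewer pregnancies and later pregnancies mean different things.

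**Working it through.** **Inputs from the protocol.** Two-sided alpha 0.05, 80% power, 142 per arm, 350 in total after 20% attrition (POWER CALCULATION AND SAMPLE SIZE). CLBR after three IVF cycles "was assumed to be 55% in the ART-only group and 71% in the surgery+ART group". ART delay of 2-3 months. Horizon of 36 months from first treatment.

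**Reproducing the plan's own figure.** n = [1.96·√(2·p̄·(1−p̄)) + 0.8416·√(p₁(1−p₁) + p₂(1−p₂))]² / (p₂−p₁)², with p₁ = 0.55, p₂ = 0.71, p̄ = 0.63:
- 1.96·√0.4662 = 1.338
- 0.8416·√0.4534 = 0.567
- (1.338 + 0.567)² / 0.16² = 3.629 / 0.0256 = 141.8, so 142 per arm, as stated.
- 284 / 0.80 = 355, close to the stated 350.

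**Assumptions, because the protocol gives no figure.** The 55% and 71% are live-birth rates borrowed for CPR. Timing of ART pregnancies was varied: truncated exponential with scale 5, 8 or 12 months (a smaller scale is more front-loaded), discrete cycles, and uniform over follow-up. There was no dropout and the log-rank was unstratified. A separate cycle-based run, stratified over four centres, gave 54.4% power for log-rank against 80.0% for proportions, in line with the cycle row below.

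**Results at 142 per arm with no early spontaneous pregnancies** (each cell: 2-month / 3-month delay).

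| Timing | Log-rank rejection, 55% vs 55% | Log-rank power, 55% vs 71% | Loss against proportion test (points) |
| --- | --- | --- | --- |
| Scale 5 | 12% / 17% | 43% / 30% | 37 / 50 |
| Scale 8 | 9.0% / 11.0% | 52.7% / 43.7% | 27.5 / 37.7 |
| Scale 12 | 6.0% / 8.2% | 60.9% / 52.7% | 19.5 / 27.8 |
| Cycles | 9% / 11% | 54% / 47% | 26 / 33 |
| Uniform | 5.3% / 5.9% | 72.8% / 68.4% | 8.3 / 11.7 |

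For scales 8 and 12 and uniform timing, the loss is the proportion test's simulated power in the same run minus that of log-rank (scale 8, 2 months: 80.2 − 52.7 = 27.5). For scale 5 and cycles it is taken from 80%. The proportion test rejects in 4-6% of trials at equal rates and has about 80% power throughout. At an assumed 65% in both arms with scale 8, log-rank rejects in 11-18%. Except under uniform timing, nearly all rejections at equal rates go against surgery. With no delay the loss is only about 3-4 points, so the delay drives the result.

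**Adding undelayed spontaneous pregnancies in the surgery arm** (15% and 30% of that arm's pregnancies, assumed).
- Scale 8: the loss falls to between 13.0 points (80.7 − 67.7; 30%, 2 months) and 29.2 points (79.9 − 50.7; 15%, 3 months).
- Scale 12: the loss is between 2.6 points (80.0 − 77.4) and 18.2 points (80.2 − 62.0).
- Uniform: the loss vanishes or reverses. At 30% and a 2-month delay, log-rank has 89.5% power against 80.4%.
- At 30%, rejection at equal rates is close to 5-7% in all three.

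**At 175 per arm with no spontaneous pregnancies**, the loss is about 19-54 points with front-loaded timing and 8-10 with uniform timing.

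**The case against.** The strongest reply is that the paragraph is headed as time-to-event analysis and is the only place that can serve the listed outcomes of time to pregnancy and time to live birth. For those, log-rank and Cox are conventional, and a rejection caused by delay is a true finding. That stands, and it is why the methods should stay for those outcomes. It does not supply a test for the CPR proportion.

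Second, the background says that "the number of spontaneous pregnancies is high after surgery on patients with deep endometriosis". CPR counts all confirmed pregnancies, so conception before ART can offset the delay. That also stands: crossing hazards are plausible but not established, and the loss shrinks or disappears in some settings.

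Third, the simulation has no dropout, while the plan allows for 20% attrition. Time-to-event methods use partial follow-up; a raw proportion needs a rule for missing outcomes. This is fair, and a 36-month Kaplan-Meier difference answers it.

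Fourth, the Kaplan-Meier curves would show a late catch-up, and checks of proportional hazards usually belong in a SAP, which was not available. But the curves are for display and do not test the three-year difference. The mismatch is also not an omitted detail: the protocol itself names both the definition and the method.

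A reader might infer that the live-birth Cox analysis is equally faulty and should be dropped. The documents do not support this. The three-year live-birth proportion is already compared as the primary analysis, and time to live birth is a listed outcome in its own right.

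**Conclusion.** The mismatch holds for CPR. It is defined as a three-year proportion and given only a test of whole curves and a hazard ratio, in a design that delays ART in one arm. Whatever the timing, the planned test cannot separate fewer women pregnant by three years from women pregnant later.

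The size is uncertain. At 142 per arm, a 2-3 month delay and borrowed rates of 55% and 71%, log-rank loses between nothing and about 50 points of power. The loss is about 20-38 points under cycle-based timing or exponential timing with scale 8 or 12, before any spontaneous pregnancies. At equal rates it rejects in about 5-18% of trials in the settings examined. It would be tempting to say that the test rejects for delay alone, or that it always loses at least 20 points. Neither is a property of the plan: both depend on assumed timing and on an unstated share of spontaneous pregnancies, and most trials with equal rates would not reject.

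The primary CLBR comparison is untouched and the protocol treats secondary endpoints as exploratory, so the consequence is confined to what can be concluded about CPR. The change is still worth making before results are seen.

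**What to change.** In Time-to-Event outcomes, state that CPR, taken as the proportion of women with at least one ultrasound-confirmed pregnancy within 36 months of first treatment, is compared by a risk ratio from the same model as the primary endpoint, with the risk difference alongside. If censoring has to be handled, use the difference in 36-month Kaplan-Meier cumulative incidence instead.

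Assign the stratified log-rank test and the Cox model explicitly to time to pregnancy and time to live birth. Keep the Cox analysis for live birth, but label it time to live birth and not CLBR. Restricted mean time to event up to 36 months is an optional supplement: it does not need proportional hazards and expresses the delay in months.

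The cost is a change of wording and a small extra analysis, with no new data or patients. The downside is that the hazard ratio is no longer the summary for CPR, so comparison with publications reporting one would rest on the time-to-pregnancy analysis.

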**Cycle-Specific Outcomes**

Live birth and pregnancy rates per IVF/ICSI cycle will be analyzed using log-binomial regression or modified Poisson regression with robust variance to account for within-patient correlation. Other cycle-specific outcomes (e.g. number of oocytes retrieved, fertilization rate, embryo transfer characteristics, miscarriage rates) will be summarized descriptively and compared between groups using appropriate regression models.

**Quality of Life and Health Status Measures:**

**EHP-30 (continuous, 0–100 scale):**
Analyzed using a linear mixed-effects model (LMM) with random intercepts for participants. Fixed effects will include treatment group, time, and the treatment×time interaction, adjusting for prespecified covariates (age, BMI, AMH, center).

**EQ-5D (continuous index 0–1):**Analyzed using the same LMM framework as EHP-30 (random intercepts, treatment, time, treatment×time, prespecified covariates).

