# PATIENT REPORTED OUTCOMES (PROMS)

When evaluating quality of life among women with endometriosis many different scales have been used, mostly of generic character that are not specific to the disease. One of these is 30-item Endometriosis Health Profile (EHP30), a scale that perform well in clinical practice in the routine evaluation of Health-Related Quality of life (HRQoL) The use of EHP30 is recommended by the National Board and Welfare in Sweden, the ASRM and ESHRE (40). Using EHP-30, a small study has shown an improvement in HRQoL in the follow-up after endometriosis surgery, an effect that may last for up to 6.8 years (41). Two recent studies show postoperative improvement in HQQoL measured by EHP-30 10 weeks and 3 months after surgery, respectively (42, 43). Especially women with deep endometriosis (DE) showed a more significant benefit from surgery (43). However, HRQoL can also be affected by infertility, and in this trial, infertility treatment will be delayed, thus, HRQoL is an important measurement.

POINTS OF ASSESSMENT

Baseline assessment will be obtained after randomization and maximum 1 month prior to surgery or start of first ART cycle

Thereafter assessment will be done prospectively at:

- 2 months after surgery (for the group randomized to first line surgery)
- 1:st oocyte pick up (for both randomization groups)
- 2 months after 1:st oocyte pick up
- 2:nd oocyte pick up
- 2 months after 2:nd oocyte pick up
- 3:rd oocyte pick up
- 2 months after 3:rd oocyte pick up
- Visit, phone call or questionnaire 3 years after randomization.

Compliance with completing the questionnaires will be investigated at each time point to

evaluate the procedure for data collection and the feasibility of the questionnaires.

INSTRUMENTS

The core questionnaire in EHP -30 includes 30 questions in 5 health-related areas: pain, control and powerlessness, emotional well-being, social support, and self-image. In addition, there are six supplementary modules covering work, relationship with child/children, sexual relationship, feelings about the medical profession, feelings about treatment and feelings about infertility.

The Numeric Rating Scale (NRS) is a frequently utilized pain assessment tool commonly employed in postoperative care. It allows for the momentary evaluation of pain on a scale from 0 to 10, with 0 representing "no pain" and 10 indicating "the worst pain imaginable”.

EQ-5D is a standardized non-disease specific instrument for describing and

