**NRS pain (ordinal: mild 1–3, moderate 4–6, severe 7–10):**
Analyzed using a generalized linear mixed model (GLMM) with cumulative logit link (ordinal logistic regression), including random intercepts for participants, fixed effects for treatment, time, and treatment×time, and prespecified covariates (age, BMI, AMH, center).

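### Random-intercept-only models for EHP-30 and EQ-5D can understate the standard error of the three-year change-from-baseline (treatment×time) term; the plain arm difference at three years is nearly unaffected

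*Protocol*

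**What the plan says.** Under Statistical Considerations, Quality of Life and Health Status Measures, the protocol says EHP-30 will be "Analyzed using a linear mixed-effects model (LMM) with random intercepts for participants". It adds: "Fixed effects will include treatment group, time, and the treatment×time interaction". The adjustment covariates are age, BMI, AMH and center; the baseline score is not among them. EQ-5D is "Analyzed using the same LMM framework as EHP-30 (random intercepts, treatment, time, treatment×time, prespecified covariates"). NRS pain uses a "generalized linear mixed model (GLMM) with cumulative logit link (ordinal logistic regression), including random intercepts for participants". None of the three models names a random slope, a serial term, an unstructured covariance or a robust variance. The Cycle-Specific Outcomes paragraph, by contrast, names robust variance to deal with within-patient correlation.

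The Patient Reported Outcomes section sets the schedule. The first reading is fixed by "Baseline assessment will be obtained after randomization and maximum 1 month prior to surgery or start of first ART cycle". Readings then follow two months after surgery (surgery arm only), at each of up to three oocyte pick-ups, two months after each pick-up, and once at three years. That is up to nine readings in the surgery arm and eight in the ART arm. The Secondary Objectives ask for a comparison of quality of life and pain between the arms, including at the three-year visit. The protocol does not say whether time is categorical or continuous, or which model term is the three-year treatment effect.

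**The concern.** A random intercept alone gives a linear model one variance and one correlation for every pair of readings. The schedule is a cluster of closely spaced readings with one isolated reading at about 36 months. The close pairs dominate the single estimated correlation, and the model then applies it to the longest gap. Surgery, stimulation and often pregnancy and birth fall between the first and last reading, so equal correlation at 2 and 36 months is doubtful.

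Because the baseline score is not a covariate, the first reading most naturally enters as a level of time, and the three-year treatment×time term becomes a difference in change from baseline. If the true correlation over 36 months is below the fitted one, that term gets an SE that is too small, a confidence interval that is too narrow, and a test that rejects too often. Changes over short gaps get intervals that are too wide.

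The covariance also matters for missing data. The Additional analysis paragraph relies on maximum likelihood under missing at random, and that protection depends on a correct covariance. Second and third pick-up readings exist only for women who need further cycles, so the data are unbalanced by design.

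**Working it through.** **Inputs.** The protocol gives no SD, correlation or SE for these scales, so there is no stated figure to reproduce on this point. The number per arm comes from its sample size calculation (55% against 71%, two-sided 5%, 80% power):

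n = [1.96·√(2·0.63·0.37) + 0.8416·√(0.55·0.45 + 0.71·0.29)]² / 0.16² = (1.338 + 0.567)² / 0.0256 ≈ 142 per arm, as stated.

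All correlations, visit times and shares of women with one, two or three cycles below are assumptions. Each reading has variance 1 unless noted.

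**Formulas, complete data, categorical time, n per arm.**
- Arm difference at one visit: SE = √(2/n). No correlation enters.
- Treatment×time term against baseline: SE = √(4(1−ρ)/n), where ρ is the correlation between the two readings. The random-intercept model uses one ρ, roughly the average over all pairs, whatever the gap.
- Real size of a nominal 5% test: 2·[1 − Φ(1.96·r)], with r = model SE / true SE.

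**Worked case.** Assume correlation about 0.78 at 2 months falling to 0.42 at 36 months. The fitted common correlation is 0.578.
- Model SE = √(4·0.422/142) = 0.109.
- True SE = √(4·0.578/142) = 0.128.
- r = 0.855; real size = 2·[1 − Φ(1.676)] = 9.4%.
- Arm difference at 36 months: √(2/142) = 0.119 under both, r = 1.00, size 5%.
- Change to first pick-up: model 0.109, true 0.0815, r = 1.34, size 0.9%.

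**Range under decaying correlation, categorical time.** The unbalanced case has 175 per arm, 40/25/35% with 1/2/3 cycles and 20% missing at three years.

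| Correlation at 2 → 36 months | Three-year change term, complete: r (size) | Three-year change term, unbalanced: r (size) | Three-year arm difference, unbalanced: r (size) | Change to first pick-up, complete: r |
|---|---|---|---|---|
| 0.79 → 0.56 | 0.88 (8.4%) | 0.86 (9.4%) | 0.98 (5.5%) | 1.23 |
| 0.78 → 0.42 | 0.86 (9.4%) | 0.82 (10.7%) | 0.97 (5.8%) | 1.34 |
| 0.75 → 0.23 | 0.84 (9.9%) | 0.81 (11.4%) | 0.96 (6.0%) | 1.41 |

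**Other cases.**
- True equal correlation (0.6 throughout): r = 1.00 for every contrast.
- Linear time with decay: slope interaction r = 0.65-0.74, size 15-21%; arm difference at 36 months r = 0.91-0.96, size 6-8%.
- Individual slopes that make variance grow, categorical time: three-year change term r = 0.84-0.92; arm difference r = 0.85-0.93, size 7-10%.
- Readings at months 0, 4, 6, 11, 13 and 36, half without a second pick-up, 20% missing at three years: with correlation about 0.75 at 4 months falling to 0.37-0.53, the change term has r = 0.78-0.81 and size 11-12.5%. With mild decay (0.79 to 0.70), r = 0.89 and size 8%.
- Further large-sample runs under decay gave r = 0.75-0.85 (size 10-14%) for the three-year change term, 1.10-1.28 for the first post-baseline change, and 0.95-0.98 (size 5-6%) for the three-year arm difference.

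**Simulation check.** In 300 simulated mixed-model fits, the three-year change term had r = 0.90 and rejected in 9.0%. The arm difference had r = 1.00 and rejected in 6.3%. Monte Carlo error is about 1.3 points at 5%.

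**The case against.** A reader might infer that the three-year treatment comparison as such has SEs that are too small. The documents do not support this. The Secondary Objectives ask how the arms compare at the three-year visit, most naturally a difference between arms at one time point. With categorical time and equal variances that difference hardly depends on the assumed correlation. The protocol never names a change-from-baseline contrast. This part of the objection stands and limits the point.

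It also stands that decay is an assumption, that equal correlation would make every SE right, and that the ordinal pain model was not simulated. In that model equal correlation applies on the latent scale, so direction and size are by analogy only.

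It can further be said that covariance structure belongs in the statistical analysis plan, that naming random intercepts does not rule out a serial term, and that sensitivity analyses for alternative modelling are promised. This stands only in part. The protocol lists the components of the framework in its EQ-5D line and includes random intercepts as the only correlation term, so a programmer following it would fit exactly that. The promised sensitivity analyses are generic and name nothing for these models.

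**Conclusion.** The point holds in a conditional and minor form. A random intercept as the only correlation term is a poor match for clustered early readings plus one at three years. If correlation decays, the SE of the three-year change-from-baseline term is about 10-25% too small with categorical time (real size about 8-14%), and 26-35% too small for a linear-time slope. Early change contrasts are too wide. The plain three-year arm difference with categorical time keeps a real size of 5-6%, rising to 7-10% only if variance grows over time.

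These sizes rest on assumed correlations and visit patterns. The primary endpoint, sample size and data collection are untouched, and the protocol treats secondary endpoints as exploratory. Their confidence intervals will still be reported and read.

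**What to change.** In Quality of Life and Health Status Measures:
- State that time is categorical.
- Name the three-year contrast: the arm difference at three years, or the difference in change from baseline.
- Replace the random-intercept-only structure by a random intercept plus a serial (spatial-power) term on actual assessment dates, or by an unstructured covariance where the visit cells allow.
- Name participant-clustered robust SEs as the fallback. They repair the SE but not the reliance of the missing-data handling on the covariance, so they should not be the first choice.

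In the NRS pain paragraph, report participant-robust SEs as a precaution.

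The cost is wording, model code and a few more covariance parameters; nothing changes in data collection. Non-convergence is possible because visits are event-driven and late cells are sparse. A full unstructured matrix over nine readings has 9·10/2 = 45 parameters, which is why the serial term is the safer first choice. The reading two months after surgery exists in one arm only and carries no treatment contrast.
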